#### Endothelium dependent dilation

Endothelium Dependent Dilation (EDD) will be assessed via brachial artery flow-mediated dilation (FMD) using high-resolution ultrasonography (Canon Xario 200G), as previously described (34). Participants will be asked to avoid exercise, caffeine, and alcohol for 24 hours, and food for at least 5 hours prior to their visit. FMD will be assessed by measuring the brachial artery diameter and blood velocity at baseline and for 3 minutes following reactive hyperemia which stimulates NO release. Reactive hyperemia is induced by 5 minutes of forearm blood flow occlusion with a cuff placed on the upper forearm and inflated at least 50 mmHg above systolic BP (26, 35). Brachial artery diameter and blood velocity will be analyzed offline using commercially available software (Brachial Analyzer, Medical Imaging Applications LLC, Coralville, IA, USA) (26) and expressed as absolute (mm) and percent change in arterial diameter from baseline (pre-cuff inflation diameter) to post-intervention following the 6 weeks of IMST.

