The potential for IMST to elicit cardiometabolic adaptations in diabetic patients warrants assessment. Accordingly, we outline a plan to interrogate the effects of 6 weeks of high-resistance IMST on glycemia (fasting plasma glucose), insulin sensitivity/resistance (fasting serum insulin and Homeostasis Model Assessment [HOMA-IR; ratio of fasting insulin/glucose]), resting BP, and NO-mediated EDD in T2DM patients. Participants will be randomized into either high-resistance (experimental) or low-resistance (control) groups, and complete IMST at home 5 days/week for 6 weeks, with each session lasting ~5 minutes (26). Participants will perform at either high relative resistance (75% of maximal inspiratory pressure in cmH_2_O, (PI_max_)) or low relative resistance (15% of PI_max_) (26). As this is a blinded study, the 15% will ensure participants feel a resistance, but there are not consistent cardiovascular improvements established in previous studies (17, 27, 28).

We will study T2DM patients before and after 6 weeks of high-resistance IMST to test the hypotheses that (1) fasting plasma glucose will decrease, and insulin sensitivity will improve, (2) resting systolic BP will decrease, and (3) high-resistance IMST will improve EDD resulting in clinically-meaningful improvements (i.e., >1% unit change) (29). We will obtain consent to collect blood DNA for banking and plasma for quantitative proteomics analysis. This will allow us to investigate novel protein expression changes before and after IMST. Omic technologies, such as proteomics, provide powerful tools for identifying biomarkers and developing new treatments (30, 31). Our study aims to use quantitative proteomics analyses to identify potential associations and putative markers related to the effects of IMST, which remain largely unexplored. We anticipate observing changes in protein abundance associated with metabolic and cellular processes following IMST, particularly in relation to outcomes in T2DM. However, it is important to note that this exploratory experiment focused on associations rather than mechanisms.

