### Participant timeline

The timeline for participation in the study will be 7-9 weeks as shown in **Figure 1**. A summary of the visits for the DIT study participants is shown in **Table 2**.

**Table 2 T2:** Summary of the visits for the DIT study.

	Baseline		Training	End-Intervention	
	Visit 1	Visit 2	Week 1-6	Visit 1	Visit 2
Screening					
Informed Consent	X				
Demographics	X				
Medical History	X				
Inclusion/Exclusion	X				
Hip/waist/neck circumference	X			X	
Functional Assessments					
Resting BP	X		X	X	
PI_max_	X		X	X	
Spirometry	X			X	
Blood Draw					
Metabolic panel		X			X
Plasma/DNA		X			X
Arterial Assessments					
FMD_BA_	X			X	
At-home Testing					
Sleep/exercise diary			X		
Exercise sessions					
Daily exercise			X		
Once-weekly supervised exercise session*			X		
Weekly text/email			X		
Randomization		X			

BP, Blood Pressure; FMD_BA_, Flow-mediated dilation of brachial artery; PI_max_, Maximal inspiratory mouth pressure. *, At this weekly supervised training session, the participant will do a fasting plasma glucose check immediately before and after the training session.

Participants will sign a written informed consent with a member of the research team at the CATS facility. Following informed consent, participants will complete all baseline assessments in two in-person visits to the CATS facility within a 14-day window. Participants will begin the 6-week intervention ≤ 14 days after baseline assessments are completed. If the participant is unable to make one of their in-person training sessions, they will proceed to do their exercises at home and come the following week for their regularly scheduled training session in order to maintain the 6-week training regimen. During the weekly training session at the CATS facility, a weekly blood pressure check will be performed (41). In addition, during the weekly visit, plasma glucose levels will be measured immediately before and after the exercise session. These measurements are exploratory and aim to identify any immediate effects of IMST on plasma glucose levels. All assessments will be repeated within 14 days after completion of the 6-week training program. Participants will continue to perform IMST 5 days/week until all post assessments are completed.

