### Power analysis and sample size

A minimum of 16 and a maximum of 24 participants will be enrolled and randomized into groups. To our knowledge, the effect of IMST on fasting glucose and/or insulin sensitivity in any population have not previously been reported, nor have effects of IMST on systolic BP and EDD in T2DM been specifically ascertained. Thus, for our power analysis we estimated a modest effect size of 0.40 with alpha set at 0.05 using a repeated measures ANOVA within-between framework. A sample size of 16-24 will have 85-96% power for any outcome with an effect size of ≥ 0.40.

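### The EDD outcome, as written, is a six-week change in arterial diameter rather than flow-mediated dilation, although the data needed for FMD are collected at both visits

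*Protocol article*

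**What the plan says.** Under Secondary outcomes, Endothelium dependent dilation, the protocol article names the method: EDD "will be assessed via brachial artery flow-mediated dilation (FMD) using high-resolution ultrasonography". It then describes the acquisition: "FMD will be assessed by measuring the brachial artery diameter and blood velocity at baseline and for 3 minutes following reactive hyperemia", with the hyperaemia produced by a five-minute forearm cuff occlusion. The last sentence of that section gives the reported quantity, which is "expressed as absolute (mm) and percent change in arterial diameter from baseline (pre-cuff inflation diameter) to post-intervention following the 6 weeks of IMST".

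The Introduction sets the target as its third hypothesis: "high-resistance IMST will improve EDD resulting in clinically-meaningful improvements (i.e., >1% unit change". Table 2 (Participant timeline) lists the brachial FMD test at the first baseline visit and the first end-intervention visit, and the text below it adds that "All assessments will be repeated within 14 days after completion of the 6-week training program". The Statistical plan analyses the data by repeated measures ANOVA.

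**The concern.** FMD is a response within one test: how far the artery widens from its resting diameter before inflation to its peak after the cuff is released. The effect of training is then the change in that response from one visit to the next. Two different baselines are involved, the pre-cuff diameter within a test and the pre-training visit within the trial.

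The article's expression starts at the first kind of baseline and ends at the second kind of follow-up. The diameter after cuff release, which carries the dilation, does not appear. What is left is a six-week change in vessel diameter, and it is unclear whether the post-training diameter is the resting one or the peak.

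EDD is one of two secondary outcomes in the abstract and the subject of one of three hypotheses. The criterion "clinically-meaningful improvements (i.e., >1% unit change" makes sense only for FMD% in percentage points. Applied to a percent change in diameter across visits, it has a different meaning. In a trial of 16 to 24 participants, a definition open to several readings also leaves room to choose among them after the data are seen.

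**Working it through.** **The plan's own figure.** The only design figure covering EDD is the power statement: "A sample size of 16-24 will have 85-96% power for any outcome with an effect size of ≥ 0.40". Its framework is "we estimated a modest effect size of 0.40 with alpha set at 0.05 using a repeated measures ANOVA within-between framework". For the group-by-time interaction with 2 groups and 2 visits, the noncentrality is λ = f² × N × m / (1 − ρ), with 1 and N − 2 degrees of freedom. The article gives no pre-post correlation, so ρ = 0.5 is assumed.

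- N = 16: λ = 0.16 × 16 × 2 / 0.5 = 10.24, power 84.5%.
- N = 24: λ = 0.16 × 24 × 2 / 0.5 = 15.36, power 96.3%.

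Both agree with the stated 85-96%. The result depends on ρ: at N = 16 and 24, ρ = 0 gives 55.8% and 75.5%, and ρ = 0.7 gives 97.0% and 99.8%. The calculation takes a standardised effect, so correcting the definition of the outcome leaves it unchanged.

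**The formulas.** Let r0 and p0 be the resting (pre-cuff) and peak post-occlusion diameters at the baseline visit, and r1 and p1 the same after training.

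- FMD% at a visit = 100 × (p − r) / r. Change in FMD% = FMD1 − FMD0, in percentage points.
- Literal reading A (resting to resting): 100 × (r1 − r0) / r0. It contains no peak and so no information on dilation.
- Literal reading B (first pre-cuff diameter to last peak): 100 × (p1 − r0) / r0. Since p1 = r1 × (1 + FMD1/100), B = A + FMD1 + A × FMD1/100. It mixes calibre change with the post-training FMD and never subtracts the baseline FMD.

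**Range of illustrations.** The documents give no diameters, so all are assumed. The baseline visit is 4.00 to 4.20 mm throughout: FMD0 = 100 × 0.20 / 4.00 = 5.0%.

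| Post visit, rest to peak (mm) | FMD1 | Change in FMD% | Reading A | Reading B |
|---|---|---|---|---|
| 4.00 to 4.20 | 5.0% | 0.0 | 0.0% | +5.0% |
| 4.00 to 4.28 | 7.0% | +2.0 | 0.0% | +7.0% |
| 4.10 to 4.305 | 5.0% | 0.0 | +2.5% | +7.6% |
| 3.90 to 4.173 | 7.0% | +2.0 | −2.5% | +4.3% |
| 4.20 to 4.284 | 2.0% | −3.0 | +5.0% | +7.1% |

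The last row in full: FMD1 = 100 × 0.084 / 4.20 = 2.0%, so the change is 2.0 − 5.0 = −3.0 points. Reading A is 100 × 0.20 / 4.00 = +5.0%, and reading B is 100 × 0.284 / 4.00 = +7.1%. In mm, FMD changes by 0.084 − 0.20 = −0.116, while the literal readings give +0.20 and +0.284.

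In these cases the literal wording can miss a gain of 2 points (row 2, reading A), show a change where FMD has none (rows 1 and 3), or reverse the sign (row 4, reading A; row 5, both readings). In every row, both readings that differ from the change in FMD% differ by more than 1 unit.

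**Fit with the planned model.** A repeated measures ANOVA with a time factor needs a value at each visit. The literal expression already spans both visits and gives one value per participant. FMD computed at each visit fits the model; the written quantity does not.

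**The case against.** The strongest reply is that nobody would follow the sentence literally. A change in resting calibre needs no cuff, no occlusion and no three-minute recording, and the parenthesis about the pre-cuff diameter shows that the authors had the FMD reference in mind. On this view two steps, FMD within a test and then its change with training, were compressed into one clause. That is probably what was meant, and the planned model supports it. But the article does not leave the formula out for the full protocol or a cited method to supply. It writes one out, and that one is wrong. The condensed format excuses omission, not a misstatement.

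A reader might infer that the trial cannot test its EDD hypothesis at all. The documents do not support this. The method is named as FMD, diameters are recorded before the cuff and during hyperaemia, the test is scheduled at both visits, and the target is set in % units. FMD% can be computed at each visit from what is collected.

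Two further limits stand. The size of the discrepancy rests entirely on assumed diameters, and nothing in the article says that resting diameter will change with training or in which direction. A calibre change equal in both arms would also largely cancel in the comparison between groups. Finally, nothing here shows the planned repeated measures model to be wrong for FMD, and the Introduction does not frame the 1-unit criterion as a difference between arms. Repairing the definition requires neither a baseline covariate nor a move of that criterion.

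**Conclusion.** The point holds as a wrongly stated outcome definition. The closing sentence of the EDD section merges a within-test reference with a between-visit contrast and omits the post-occlusion peak, so what it defines is a six-week change in diameter, not FMD. In the starkest illustration an FMD loss of 3.0 points would be reported as +5.0% or +7.1%, against a criterion of 1 unit. These figures show what the wording permits and are not a forecast of bias in this trial.

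The reach is limited: a secondary outcome of a trial that calls itself exploratory, with data collection, sample size, power and alpha untouched. It should still be corrected before analysis, because the sentence as it stands can change both the sign of the EDD result and whether it meets the criterion.

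**What to change.** Replace the closing expression in the EDD section with a definition in two steps, for example:

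*At each visit, absolute FMD (mm) is the peak post-deflation diameter minus the pre-inflation diameter of the same session, and FMD% is 100 times that difference divided by the same pre-inflation diameter. The outcome is the change in FMD (in mm, and in percentage points for FMD%) from baseline to end-intervention, compared between groups under the planned repeated measures model.*

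State beside hypothesis 3 in the Introduction that the criterion of more than 1% unit is read in FMD percentage points. A baseline-adjusted analysis may be added but is optional.

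The cost is a short rewrite of the definition and a clarifying phrase in the Introduction. The diameters, visits and analysis software are already in the plan.

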### Exploratory outcomes

#### Proteomic analysis

Blood will be collected into purple K2-EDTA vacutainers and immediately placed on ice, then centrifuged at 3,000 rpm at 4°C within 10 minutes of blood collection. Separated plasma will be removed and frozen at -80°C in cryotubes until analyzed using high-performance liquid chromatograph-electrospray ionization-MS/MS (LC-MS) (36). Briefly, the extracted plasma proteins will be subjected to subsequent in-solution digestion using trypsin and Lys-C to be analyzed with tandem mass spectrometry (36, 37). Lastly, quantitative proteomics will be performed using extracted ion abundance, including statistical analysis via Progenesis (38). The resulting quantitative proteomic data sets will be analyzed using DAVID for gene ontology and pathway enrichment analysis (39, 40).

#### DNA banking

Blood will be collected from the antecubital vein of the arm directly into PAXgene DNA collection tubes, as per manufacturer’s instructions. Briefly, these tubes contain an additive reagent that stabilizes the blood. The tubes will sit at room temperature for 2 hours then will be stored in the -20 freezer until ready to be processed. The PAXgene DNA processing kit will be used for isolation of the DNA. Once DNA is extracted, it will be stored and banked for future studies. Participants will be required to provide their consent for banking of their de-identified DNA/plasma samples.

### Participant timeline

The timeline for participation in the study will be 7-9 weeks as shown in **Figure 1**. A summary of the visits for the DIT study participants is shown in **Table 2**.

**Table 2 T2:** Summary of the visits for the DIT study.

	Baseline		Training	End-Intervention	
	Visit 1	Visit 2	Week 1-6	Visit 1	Visit 2
Screening					
Informed Consent	X				
Demographics	X				
Medical History	X				
Inclusion/Exclusion	X				
Hip/waist/neck circumference	X			X	
Functional Assessments					
Resting BP	X		X	X	
PI_max_	X		X	X	
Spirometry	X			X	
Blood Draw					
Metabolic panel		X			X
Plasma/DNA		X			X
Arterial Assessments					
FMD_BA_	X			X	
At-home Testing					
Sleep/exercise diary			X		
Exercise sessions					
Daily exercise			X		
Once-weekly supervised exercise session*			X		
Weekly text/email			X		
Randomization		X			

BP, Blood Pressure; FMD_BA_, Flow-mediated dilation of brachial artery; PI_max_, Maximal inspiratory mouth pressure. *, At this weekly supervised training session, the participant will do a fasting plasma glucose check immediately before and after the training session.

Participants will sign a written informed consent with a member of the research team at the CATS facility. Following informed consent, participants will complete all baseline assessments in two in-person visits to the CATS facility within a 14-day window. Participants will begin the 6-week intervention ≤ 14 days after baseline assessments are completed. If the participant is unable to make one of their in-person training sessions, they will proceed to do their exercises at home and come the following week for their regularly scheduled training session in order to maintain the 6-week training regimen. During the weekly training session at the CATS facility, a weekly blood pressure check will be performed (41). In addition, during the weekly visit, plasma glucose levels will be measured immediately before and after the exercise session. These measurements are exploratory and aim to identify any immediate effects of IMST on plasma glucose levels. All assessments will be repeated within 14 days after completion of the 6-week training program. Participants will continue to perform IMST 5 days/week until all post assessments are completed.

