## Discussion

Regular exercise is one of the most commonly prescribed non-pharmacological interventions for T2DM management and yields improvements in glycemic control and insulin action (6, 7). However, aerobic exercise is physically strenuous and time-consuming (10, 11) and less than half of T2DM adults participate in exercise on a regular basis. IIn contrast, IMST is a novel form of high intensity training that can be performed whether sitting or standing requires only 5 minutes per day, and rapidly improves blood pressure, endothelial vascular function, and vascular resistance among hypertensive adults (17, 18, 20, 28). Whether IMST can also affect changes in fasting blood glucose or insulin sensitivity is of critical interest and important for adults with T2DM, along with establishing if these blood pressure lowering effects and increased EDD are also seen in this population following IMST.

A study by Corrêa et al. studied the acute effects of IMST on glucose variability and showed significant improvements in glucose immediately following the training (42). Additionally, another study which was for 12 weeks at a lower resistance of 30% revealed no significant changes in blood glucose levels (43). The discrepancies across these findings are likely due to populations studied, the timeframe of the training and the resistance used. To our knowledge there have been no investigations that have reported the effects of chronic IMST training at a resistance of 75% or an interval training protocol similar to ours on glycemic control and insulin sensitivity in T2DM.

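### The primary fasting blood draw has no required gap after the last IMST session, so a possible acute effect could be mixed with the training adaptation in glucose, insulin and HOMA-IR

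*Protocol article*

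**What the plan says.** All of this comes from the protocol article.

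- **Training prescription (Introduction).** Participants are to "complete IMST at home 5 days/week for 6 weeks".
- **Post-test window (Participant timeline).** "All assessments will be repeated within 14 days after completion of the 6-week training program". The same paragraph adds: "Participants will continue to perform IMST 5 days/week until all post assessments are completed".
- **Visit placement (Table 2).** FMD is at End-Intervention Visit 1. The metabolic panel is at End-Intervention Visit 2.
- **Preparation for the blood draw (Fasting plasma glucose and fasting serum insulin).** A 12-hour fast is required before both the baseline and the post-intervention draw. Time since the last IMST session is not mentioned.
- **Preparation for FMD (Endothelium dependent dilation).** "Participants will be asked to avoid exercise, caffeine, and alcohol for 24 hours". The text does not say whether an IMST session counts as exercise.
- **Acute effect.** The Discussion cites a study that "studied the acute effects of IMST on glucose variability and showed significant improvements in glucose immediately following the training". The Participant timeline section plans glucose readings directly before and after each weekly supervised session, as an exploratory look for an immediate effect.
- **Duration (Participant timeline).** "The timeline for participation in the study will be 7-9 weeks". For the windows: "participants will complete all baseline assessments in two in-person visits to the CATS facility within a 14-day window", and "Participants will begin the 6-week intervention ≤ 14 days after baseline assessments are completed".

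**The concern.** The primary hypothesis concerns what six weeks of high-resistance training does to fasting glucose and insulin sensitivity, and the Discussion proposes an adaptation through nitric oxide. To test that, the post-intervention draw should reflect the trained state and not the hours after a session. The plan protects a secondary outcome (FMD) from recent exercise but gives the three primary outcomes no such protection.

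Baseline and post-test also differ. No IMST precedes the baseline draw, but training is still under way at the post-test draw. Any short-lived effect of a session would therefore enter the pre-post change. If it depends on resistance (75% against 15% of PImax), it would also enter the difference between arms. What is at stake is attribution: a difference in glucose or HOMA-IR could not be cleanly assigned to adaptation. With 16 to 24 participants, uneven intervals between session and draw would also add noise.

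**Working it through.** **1. Is a session shortly before the primary draw allowed?**

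| | FMD | Primary blood draw |
|---|---|---|
| End-Intervention visit (Table 2) | Visit 1 | Visit 2 |
| Food | at least 5 hours without | 12 hours without |
| Exercise | 24 hours without | nothing stated |
| IMST ongoing at post-test | yes | yes |
| IMST before the baseline measure | none | none |

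Fasting does not rule out a session. The footnote to Table 2 describes a fasting glucose check directly before and after the supervised session, so training while fasted is already part of this trial. A session on the morning of the draw is compatible with every instruction stated.

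**2. How would an acute effect enter the contrast?**

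Let C_H and C_L be the training adaptations in the high- and low-resistance arms, and a_H and a_L the acute effects still present at the draw in participants who trained shortly before. Let p be the share of participants who did so, taken as equal because both arms follow the same schedule.

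- High-arm change: C_H + p × a_H
- Low-arm change: C_L + p × a_L
- Difference between arms: (C_H − C_L) + p × (a_H − a_L)

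The last term vanishes if p = 0 or if a_H = a_L. The document gives none of p, a_H and a_L, so the term cannot be given a size. The abstention acts on p.

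HOMA-IR is insulin × glucose / 405. At unchanged insulin, an acute percentage change in glucose therefore passes into HOMA-IR in full.

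**3. Exposure at post-test**

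- Shortest: 6 weeks × 5 sessions = 30 prescribed sessions.
- Longest: (42 + 14) / 7 = 8 weeks; 8 × 5 = 40 prescribed sessions.
- Excess over nominal: 40 / 30 − 1 = 33% at most, reached only if the last assessment falls at the end of the window.

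**4. Participation time**

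The plan states 7-9 weeks. The windows in the same section are baseline 0-14 days, gap to start 0-14 days, training 42 days and post-test 0-14 days.

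| Counted from | Shortest | Longest |
|---|---|---|
| First baseline visit | 42 / 7 = 6 weeks | (14 + 14 + 42 + 14) / 7 = 84 / 7 = 12 weeks |
| Last baseline visit | 42 / 7 = 6 weeks | (14 + 42 + 14) / 7 = 70 / 7 = 10 weeks |
| First training day | 42 / 7 = 6 weeks | (42 + 14) / 7 = 56 / 7 = 8 weeks |

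None of these pairs of limits is 7 and 9. The first two ranges contain 7-9 weeks, so the stated figure may describe a typical course, but it does not describe the limits.

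Table 2 marks daily exercise only under weeks 1-6, whereas the text continues it until the last assessment. These two places also need to be reconciled.

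**The case against.** **No acute effect has been shown in this trial.** This stands. The weekly glucose readings are labelled exploratory. The Discussion describes the acute study only briefly, and also cites a 12-week study at 30% resistance with no significant change in glucose. How large an acute effect would be, how long it would last, and whether it would show in a fasted draw are all unknown. The point is therefore about a possibility that the plan leaves open.

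**Both arms follow the same schedule.** This also stands. The post-test window does not in itself bias the randomised comparison, and the contrast of the two assigned regimens remains valid. Only a difference between the arms' acute effects would enter it. What remains is whether the result can be read as adaptation.

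**Continued training is a reasonable choice and is disclosed.** Stopping at week 6 would leave up to 14 days of variable detraining. The article does not give this reason, but it is a coherent one, and the remedy below leaves the prescription alone.

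**A condensed article may omit visit instructions.** The full protocol may say more. But the article states the preparation for both visits, the two differ, and the training rule as written permits the problem. That goes beyond an omitted detail.

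**The windows are maxima, and Figure 1 is not available.** This is fair. The 7-9 week statement is a minor inconsistency and does not touch the primary contrast.

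**Conclusion.** The point holds as an inexpensive improvement to the design. As written, an IMST session may shortly precede the post-intervention draw but not the baseline draw. An acute effect, which the protocol itself treats as an open question, could then be mixed with adaptation in all three primary outcomes. This rests on two conditions that the document does not settle: that some participants train shortly before the draw, and that an acute effect persists to the draw. For the difference between arms, the effect must also differ by resistance.

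A reader might infer two stronger conclusions, and the document supports neither.

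- *That the trial will report an acute effect as a six-week effect.* No such effect is demonstrated here, so the most that can be said is that the two could not be separated.
- *That a bias in mg/dL can be stated.* Any such figure would multiply an assumed acute fall by an assumed share of participants. If it counted the high-resistance arm alone, it would also set the control arm's acute effect to zero.

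The trial's own weekly readings will show any immediate effect by arm, but not how long it lasts.

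The secondary points are descriptive: exposure at post-test is 6 to 8 weeks (30 to 40 prescribed sessions), and the windows allow about 6 to 12 weeks of participation against the 7-9 stated.

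**What to change.** 1. Apply the 24-hour exercise abstention already written for FMD to the fasting blood-draw visit, and state that it includes IMST sessions.
2. Book the draw after a non-training day, before any session that day. Five training days a week leave two free, so the prescription is unchanged.
3. Record hours since the last IMST session at the draw, and total sessions completed by then.
4. Describe exposure at post-test as 6 to 8 weeks, or 30 to 40 prescribed sessions, and reconcile the daily-exercise row of Table 2 with the text.
5. Say whether 7-9 weeks is a typical or a maximum duration and from which visit it is counted, and reconcile it with the windows.

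The cost is visit booking, two entries on the data form and some wording. The downside is slightly less freedom in scheduling the final visits.
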